### Data analysis

#### Primary analysis

The main analysis consists in calculating the local control rate at 6 months, with its 90% confidence interval, and the result will be interpreted according to Fleming’s procedure. In the case of non-assessable patients, in order to preserve power and control the alpha risk, the strategy used will be to estimate the local control rate using the Kaplan-Meier method (and to compare it to the rejection rate adjusted on the ratio between the number of assessable patients and the number of patients included).

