To date, four prospective studies on postoperative SRT have been published and have shown an estimated local control rate of 70% at 6 months and 62% at one year, with an increased risk of radio-necrosis (nearly 18% at one year) and leptomeningeal relapse (nearly 17% at one year) [9, 12–14]. A phase-III randomized study conducted on 194 patients compared WBRT to postoperative SRT [9]. With a median follow-up of 11 months, the authors showed that the survival time without cognitive deterioration was longer for patients treated with postoperative SRT than for those treated with WBRT (respectively, a median of 3.7 months [CI95 3,45-5,06] vs. 3.0 months [CI95 2,85-3,25]; HR 0,47 [CI95 0,35-0,63]; *p* < 0.0001). Furthermore, six-month cognitive deterioration was significantly less frequent for patients treated with postoperative SRT (− 33.6% [CI95–45,3-21,8]; *p* < 0.00031). No differences were found between the groups in terms of overall survival (HR 1,07; [CI95 0,76-1,50]; *p* = 0.7). However, postoperative SRT has several drawbacks: difficulties in delineating the target volume, a high volume of irradiation, a high rate of leptomeningeal recurrence and long overall treatment time (3–6 weeks between surgery and SRT). The alternative to postoperative SRT could be preoperative SRT, providing local control remains at least equivalent. This is an innovative concept that could enable the benefits of SRT to be retained with fewer drawbacks than with postoperative SRT.

To date, three retrospective series of preoperative SRT with a limited number of patients have been published and seem to confirm these advantages [15–17]. The median dose prescribed was 14 Gy (1 fraction) on isodose 80% without any margin around the metastasis. Surgery was most often carried out within 24–48 h following SRT.

A retrospective study conducted by Asher et al. on 47 patients treated with preoperative SRT showed 6-month and 12-month survival rates of 77,8 and 60% respectively [15]. The six-month local control rate was 97,8%, falling to 85,6% and 71,8% at 12 and 24 months respectively. With 12 months’ hindsight, no radio-necrosis or leptomeningeal relapse was found in the cohort.

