### Study objectives and endpoints

#### Primary objective

##### The primary objective of the STEP study is to assess 6-month local control after preoperative SRT

At the M6 follow-up visit (i.e. 6 months after preoperative SRT), local control will be evaluated on cerebral MRI. Local relapse is defined as the emergence or progression of nodular contrast within the resection cavity according to the RANO-BM criteria.

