##### Assessment of leptomeningeal relapses and assessment of cerebral distant control

This will be assessed using MRI and a clinical examination at each study time-point during follow-up (M3, M6, M9, M12).

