### Statistical analysis

#### Sample size

For sample size calculation, two elements have been taken into account: the primary objective of efficacy at 6 months and the secondary endpoint of 1-year radio-necrosis toxicity.

The efficacy of pre-operative SRT is expected to be at least equivalent to postoperative SRT, estimated at 70%. The experimental plan of the study is Fleming’s one-stage design with a sufficient efficacy threshold set at 86% (higher than rates observed in retrospective studies) and an insufficient efficacy threshold set at 70%. In order to control the (one-sided) type I error rate α at 5% and type II error rate β at 10%, the minimum number of patients to be enrolled should be 57.

For the incidence of radio-necrosis at 1 year, to conclude to a decrease compared to that induced in the case of postoperative SRT, a percentage lower than 5% (as observed in the retrospective series) will be accepted and we decided to reject proportions exceeding 15%. To ensure α < 5% and β < 20%, it is sufficient to include 59 patients. The less restrictive hypothesis in terms of power in this second Fleming’s design was decided on the basis that it concerns a secondary objective.

Thus, by including 70 patients, it is possible to compensate for a proportion of more than 15% missing data (for whatever reason) and hence to ensure adequate power of the study in terms of main objective and first secondary objective (the evaluation of the incidence of radio-necrosis).

The treatment will be considered efficacious (and therefore the trial positive) if at least 56/70 of the patients achieve local control. In this case, the estimate of the probability of success will be 80% (90% confidence interval of 71.3–86.9%, Jeffreys method), at least. The treatment will be considered to induce an acceptable level of radio-necrosis if no more than 5/70 patients have this toxicity, and, in this case, the estimate of the probability of toxicity will be 7% (90% confidence interval 3.3–13.6%, Jeffreys method), at least.

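### The claim that Kaplan-Meier controls the alpha risk holds only if a missing MRI is unrelated to local relapse, which is doubtful here

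*Protocol article*

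**What the plan says.** All references are to the protocol article.

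- **Primary objective.** At the M6 visit, "local control will be evaluated on cerebral MRI". Relapse is new or growing nodular contrast in the resection cavity under RANO-BM. The text gives no clinical event and no death component.
- **Leptomeningeal relapse and cerebral distant control.** Here the assessment has two parts: "This will be assessed using MRI and a clinical examination at each study time-point during follow-up". The local control definition has no such clinical element.
- **Data collection schedule (Table 3).** Follow-up MRI is at M3, M6, M9 and M12, so a patient has one follow-up scan before the primary time-point.
- **Sample size.** The design has "sufficient efficacy threshold set at 86"% and "an insufficient efficacy threshold set at 70"%, with one-sided alpha 5% and beta 10%. The trial is positive with 56 or more of 70 patients controlled.
- **Primary analysis.** If some patients are non-assessable, "in order to preserve power and control the alpha risk, the strategy used will be to estimate the local control rate" by Kaplan-Meier. The estimate is compared with a rejection rate adjusted by the ratio of assessable to included patients. No formula for the adjustment is given.
- **Missing data.** Values are not replaced. The nature and effect of missingness are examined if its level is significant, a level that is not defined.

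**The concern.** Kaplan-Meier gives a valid estimate under censoring only if censored patients have the same risk of relapse as those still followed. In this trial a cavity relapse can itself cause the missing scan: the patient becomes too ill to be imaged, or dies, before the relapse is seen. Such a patient has no event under the stated definition. Treated as censored, the patient is assumed to be at average risk when the relapse has already happened.

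The error runs one way. Removing relapses raises the estimated control rate and makes a positive call more likely when true control is only 70%. A single-arm trial has no control group in which the bias could cancel. The protocol's statement that the strategy controls the alpha risk is therefore a conditional statement written without its condition.

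**Working it through.** **1. The plan's own figures (Sample size section).**

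- Normal approximation for N: [(1.645 × √(0.70 × 0.30) + 1.282 × √(0.86 × 0.14)) / 0.16]² = 56.1, rounded up to 57. This agrees with the plan, which says "the minimum number of patients to be enrolled should be 57".
- Exact binomial: 46/57 or more has alpha 4.86% and power 90.6%.
- The rule 56/70 has alpha 4.13% and power 94.1%. The 90% Jeffreys interval for 56/70 is 71.3-86.9%, as stated.

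The design reproduces, so the issue lies only in what happens with non-assessable patients.

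**2. Size of the bias.** Assume true 6-month control of 70%, a constant relapse hazard, and scans at M3 and M6. Assume also that a share q of relapsers is lost before the next scan and censored at the previous one. The share q is an assumption, because the documents give none. The true probability of relapse per 3-month interval is 1 − √0.70 = 0.1633. The interval hazard that Kaplan-Meier sees is (1 − q) × 0.1633 / (1 − q × 0.1633), so the estimate tends to

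S = 0.70 / (1 − 0.1633q)²

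- q = 0: 0.700
- q = 10%: 0.70 / 0.98367² = 0.723
- q = 20%: 0.70 / 0.96734² = 0.748

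Expected relapses are 70 × 0.30 = 21, so q = 10% hides about 2 patients and q = 20% about 4.

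**3. Effect on type I error.** Simulation used 40,000 trials per scenario with N = 70. Unrelated deaths by M6 were set at 0%, 15% or 22.2%. The last value is one minus the survival in the retrospective series of 47 patients cited in Background, which "showed 6-month and 12-month survival rates of 77,8 and 60% respectively". Two thresholds were tried: a fixed 80% (56/70), and the exact 5% binomial cut-off recomputed for the number assessable. The latter is one reading of the adjusted rejection rate. Ranges are over the three death rates.

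| Relapses hidden | Mean Kaplan-Meier estimate | Type I error, adjusted threshold | Type I error, fixed 80% |
|---|---|---|---|
| 0% | 0.70 | 2.4-4.0% | 4.0-4.5% |
| 10% (about 2 patients) | 0.72 | 5.2-8.4% | 7.4-9.8% |
| 20% (about 4 patients) | 0.75 | 10.8-16.5% | 16.9-19.1% |

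A separate rerun agreed to within simulation error. The M3 scan is built in, so only relapses arising since the last scan can be hidden.

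**4. If the hidden relapsers are counted as failures,** type I error returns to 2.4-4.2% (adjusted) or 3.9-4.7% (fixed 80%).

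**5. What a broader failure rule would cost as the primary rule.** Suppose d of 70 patients die neurologically of non-local disease, independently of local control, and are counted as local failures. Power at 86% is then P(Bin(70 − d, 0.86) ≥ 56): 85%, 78% and 68% for d = 2, 3 and 4, against 94.1% for d = 0.

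**The case against.** **Censoring is inferred.** The article does not say that these patients are censored. It names the method, and the full protocol or an analysis plan not shown could define them as failures. This stands. A reader might infer that the plan is known to discard these relapses; the text supports only that censoring is the ordinary consequence of Kaplan-Meier with an MRI-defined event. What remains open to criticism is the unconditional claim about alpha, which is in the text.

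**Kaplan-Meier does not break alpha as such.** This also stands: with unrelated censoring, type I error was 2.4-4.5%.

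**The number of hidden relapses is unknown.** At 77.8% survival, 70 × 0.222 gives about 15 deaths by M6, and it is tempting to conclude that 2 to 4 hidden relapses are likely. That does not follow. The documents give no share of neurological deaths, and no share due to the cavity. The series is small and retrospective. The trial also requires Karnofsky status of at least 70 and estimated survival of at least 6 months. Nothing bars an unscheduled MRI in a deteriorating patient, and the RANO-BM criteria are not reproduced in the article.

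**Existing safeguards.** The Missing data section does promise to examine the nature of missingness, but only at a significant level. Two patients are 3% of 70 and could fall below it. The adjusted threshold offsets part of the bias on the reading tried, not all of it.

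**A literal 56/70.** Counting everyone not shown to be controlled as a failure keeps type I error at or below about 4.2%. Power at 86% control, however, falls to about 12% with 15% deaths and about 1% with 22.2%. That defeats the section's own aim of preserving power, so it is unlikely to be the intended rule.

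**Conclusion.** The point holds as a missing condition on a stated claim. Control of the alpha risk depends on non-assessability being unrelated to local relapse. With an MRI-only event and a disease that can prevent the scan, that is doubtful, and any departure of this kind favours a positive trial.

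At true control of 70%, about 2 unseen relapses in 70 patients are enough to exceed 5% (about 5-8.5% with the adjusted threshold as read here, 7-10% with a fixed 80%). About 4 give 11-19%. These figures rest on an assumed hidden share, a constant relapse hazard, censoring at the previous scan, and one reading of an adjustment whose formula is not given. They show sensitivity and do not predict the error rate of this trial.

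A reader might go further and make every neurological death a local failure in the primary analysis. The documents do not support that: leptomeningeal and distant relapse are separate endpoints, and the rule would charge deaths from them to local control at the cost in power shown above. How the studies behind the 70% benchmark handled deaths is not stated either.

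**What to change.** 1. In Primary analysis, keep Kaplan-Meier and state that alpha control is conditional on non-informative censoring.
2. State how death and neurological deterioration before the M6 MRI enter the local control estimate, and reconcile this with the 56/70 rule.
3. Pre-specify, whatever the level of missing data, a sensitivity analysis counting as local failures the patients who die of a neurological cause, or become non-assessable through neurological deterioration, with no later MRI.
4. Add a worst case with all non-assessable patients as failures. Report whether the success call survives each analysis.
5. Record in the eCRF whether each death was neurological.

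The cost is a few sentences, one eCRF field and the extra analyses. Both sensitivity estimates are conservative, the first because some neurological deaths come from distant or leptomeningeal disease. The worst case must fail once 15 patients are non-assessable, since 70 − 15 = 55 is below 56, so it is a bound. Neither should replace the primary rule.

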#### Missing data

Missing data will not be replaced (it will be managed by partial elimination). If there is a significant level of missing data, an analysis will be performed to assess its statistical nature and its potential effect on the results. If relevant, an appropriate method of imputation will be envisaged.

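### The primary success rule is not uniquely defined once a patient is non-assessable, and the ratio adjustment of the rejection rate is either redundant or breaks the error control it claims

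*Protocol article*

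**What the plan says.** The Protocol article, Sample size, sets up a one-stage Fleming design with "an insufficient efficacy threshold set at 70"% and a "sufficient efficacy threshold set at 86"%. It aims to "control the (one-sided) type I error rate α at 5% and type II error rate β at 10"%, and from this derives that "the minimum number of patients to be enrolled should be 57". Seventy are to be included, to absorb somewhat more than 15% missing data. The decision rule is: "The treatment will be considered efficacious (and therefore the trial positive) if at least 56/70 of the patients achieve local control".

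Primary analysis adds a second rule for the case where some patients cannot be assessed. The rate is then estimated by Kaplan-Meier, and the analysis will "compare it to the rejection rate adjusted on the ratio between the number of assessable patients and the number of patients included". The reason given is to protect power and the type I error.

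Missing data, which covers the study in general, says: "Missing data will not be replaced (it will be managed by partial elimination"). Imputation is left open.

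**The concern.** A Kaplan-Meier estimate of 6-month local control is on the same scale as the 80% that 56/70 represents. Under non-informative censoring it already accounts for patients who leave observation early. Moving the bar by the ratio of assessable to included patients therefore corrects a second time for the same loss.

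The sentence also does not say which rate is the rejection rate, whether it is multiplied or divided, or whether the rate or the count is adjusted. These choices give very different tests, and this is the go/no-go rule for the primary endpoint. Some non-assessability is to be expected: the one preoperative series for which Background quotes survival "showed 6-month and 12-month survival rates of 77,8 and 60% respectively". If the reading is chosen after the data are seen, that choice could decide the trial.

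**Working it through.** **Inputs.** From Sample size: null 0.70, alternative 0.86, one-sided alpha 5%, power 90%, minimum n 57, planned n 70, cut-off 56. Let m be the number assessable out of 70.

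**The plan's own figures reproduce.** For X ~ Binomial(n, p):
- n = 57, cut-off 46: P(X ≥ 46 | 0.70) = 0.049 and P(X ≥ 46 | 0.86) = 0.906.
- n = 70, cut-off 56: alpha 0.041, power 0.941. A cut-off of 55 gives alpha 0.073, so 56 is the smallest valid one.
- Jeffreys 90% interval at 56/70, from Beta(56.5, 14.5): 71.3–86.9%, as stated.

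**Reading A: the rate is multiplied by the ratio.** Bar = 0.80 × m/70; smallest passing count r = m × bar, rounded up; alpha = P(X ≥ r | m, 0.70).

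| Non-assessable | m | Bar | r | Alpha |
|---|---|---|---|---|
| 1 | 69 | 78.9% | 55 | 0.048 |
| 2 | 68 | 77.7% | 53 | 0.095 |
| 4 | 66 | 75.4% | 50 | 0.189 |
| 7 | 63 | 72.0% | 46 | 0.356 |
| 8 | 62 | 70.9% | 44 | 0.496 |
| 9 | 61 | 69.7% | 43 | 0.530 |
| 11 | 59 | 67.4% | 40 | 0.700 |

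Eleven of 70 is 15.7%, and the 57 needed for the primary endpoint corresponds to 13/70 = 18.6% missing. The whole table is therefore inside the range the trial plans for. A Kaplan-Meier simulation (exponential time to relapse, non-assessable patients censored uniformly over 0–6 months, 20,000 runs) gives similar values: 0.082 at m = 68, 0.152 at 66, 0.448 at 62 and 0.677 at 59.

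**Reading B: the rate is divided by the ratio.** Bar = 0.80 × 70/m = 56/m, which reaches 100% at m = 56. In a second simulation (70 patients, MRI at M3 and M6, constant hazards, non-informative death, 20,000 trials), power at true control of 86% is about 71% for 6-month survival of 95% and 36% for 90%. Both survival values are assumptions.

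**Reading C: only the count of 56 is scaled.** The required count is 56 × m/70 = 0.80 × m, so the bar stays at 80%. Exact alpha for m from 57 to 70 lies between 0.026 and 0.057 (for example 0.041 at 66, 0.057 at 60, 0.035 at 59). On the rate scale nothing has been adjusted.

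**Rules without the ratio**, in the second simulation, over assumed 6-month survival of 95%, 90%, 85% and 77.8%:
- Kaplan-Meier estimate of at least 80%: alpha about 3–4%, power about 90–92%.
- Lower limit of the two-sided 90% log-log interval above 70%: alpha about 4%, power about 89–93%.

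Re-deriving the exact Fleming cut-off for the number assessable gives the same message. It is 53/66 (80.3%), 50/62 (80.6%), 48/59 (81.4%) and 46/57 (80.7%). A bar that controls alpha stays near 80–82% and does not fall as patients are lost.

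**The case against.** The strongest reply is that the plan never says it multiplies 80% by the ratio. It gives no base rate, direction or formula, and Sample size does not call 80% the rejection rate. Because the stated purpose is error control, a sympathetic reader would choose Reading C, which nearly achieves it. This stands: a reader might infer that the plan has definitely lost its 5% type I error, and the text does not establish that. Reading A is the most direct one only because the quantity compared is a rate and the quantity adjusted is a rate.

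It is also fair that an article condenses the full protocol, and a formula may be given there. But the article does state a decision rule and claims a property for it. On a Kaplan-Meier scale that rule is either empty or harmful, which goes beyond omitted detail.

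A reader might further see three conflicting treatments of the same patients: the fixed 56/70, the Kaplan-Meier rule and partial elimination. That goes too far. The first applies when all 70 count, the second is specific to non-assessable patients, and a specific rule ordinarily governs over a general one. What remains is that the Missing data section does not exempt the primary endpoint.

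**Conclusion.** The point holds as a defect in how the primary decision rule is defined. At 11 of 70 non-assessable, one-sided alpha is 3.5% if the count is scaled and 70% if the rate is multiplied, from the same sentence. If the rate is divided, the loss is in power.

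Two stronger statements are not supported. The bar does not fall below the 70% null whenever a patient is missing: even on Reading A this needs at least 9 of 70, although alpha already exceeds 5% from 2. Nor should the most extreme results be taken as expected. With 77.8% survival, Reading A declares an ineffective treatment positive in about 81% of simulated trials and Reading B has about 1% power. Those figures borrow mortality from one retrospective series of 47 patients, whereas STEP requires an estimated survival of at least 6 months and a Karnofsky status of at least 70.

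The exact alphas treat the estimate as a proportion among those assessable. The simulations assume constant hazards and censoring unrelated to relapse.

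**What to change.** Delete the ratio adjustment from Primary analysis and state one rule. For example: 6-month local control is the Kaplan-Meier estimate in all included patients who start SRT, and the trial is positive if the lower limit of the two-sided 90% confidence interval exceeds 70%. Name the interval type. Log-log performs as shown above, but it is one valid choice among several. An unscaled 80% Kaplan-Meier bar performs similarly, and a Fleming cut-off re-derived for the number assessable would also be a defined rule.

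Add to Missing data that partial elimination does not apply to the primary endpoint.

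The cost is wording only, with no extra patients or visits. The stated power may read about 89–90% if 6-month mortality is as high as 22%. The change should be made before the primary data are examined.

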#### Secondary analyses

The objectives involving descriptive analyses will call on conventional methods: an evaluation of different toxicities at different times using percentages and confidence intervals. The analysis of survival data (evaluation of local control, distant control, and overall survival) will be carried out using the Kaplan-Meier method (estimation of survival rates at different times with confidence intervals based on cumulative hazard), and Cox proportional hazards model (uni- and multivariate regression, possibly LASSO-penalized) to search for predictive factors. To investigate predictive factors for complications, a univariate analysis will be performed first, followed by a multivariate logistic regression (penalized if necessary).

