#### Secondary objectives

##### Assessment of local control at 1 year

At the M12 follow-up visit (i.e. 12 months after preoperative SRT), local control will be evaluated on cerebral MRI.

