#### Participant eligibility

The inclusion and non-inclusion criteria are presented in Table 1. Patients will be eligible for the study if they have no more than 4 distinct brain metastases, including one with a surgical indication, an indication for SRT and surgery, and no contraindication for MRI. They will be ineligible if they have metastases from sarcoma or small-cell lung cancer, if they have a documented leptomeningeal disease, or if their survival is estimated under 6 months according to the DS GPA (diagnosis-specific graded prognostic assessment).

**Table 1 Tab1:** Selection criteria

Inclusion criteria	Non-inclusion criteria
≤ 4 distinct brain metastases, one with surgical indication	Lymphoma, leukaemia, multiple myeloma, germinal tumours or cerebral primary cancer
Diagnosis of histologically proven breast, digestive, non-small cells lung cancer, kidney or melanoma	Metastases from small-cells lung cancer or sarcoma
≤ 5 cm larger diameter	Mass effect with deflection ≥5 mm from median line or hydrocephaly or compression 4th ventricle, patient neurologically unstable, need for emergency decompressive surgery
Karnofsky performance status ≥70	> 4 brain metastases
No contraindication for MRI	Contraindication to anaesthesia, MRI or gadolinium injection
Possibility for the patient to be treat with both surgery and stereotactic radiotherapy	Proximity of the tumour with organs at risk which do not allow the prescribed dose to be reached in the envelope
≥ 18 years old	Pregnant or breastfeeding woman
Estimated overall survival ≥6 months according to DS GPA	Anti VEGF within 6 weeks before treatment
Written inform consent signed	Documented leptomeningeal injury
Affiliation to the French social security system	History of irradiation of the encephalon in toto
For women of childbearing age including those on LH-RH agonists for ovarian suppression: inclusion negative serum pregnancy test (≤ 7 days prior to the start of preoperative RSH).	History of stereotactic radiotherapy on metastasis to be operated on
	Non-candidate patient for surgery
	Surgical delay > 3 days compared to stereotactic radiotherapy
	Estimated survival < 6 months by DS GPA
	Patient under guardianship or curatorship
	Psychological disorder (cognitive disorders, mental alertness, etc.) or social (deprivation of liberty by judicial or administrative decision) or geographical reasons that may compromise medical monitoring of the trial or compliance with treatment

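### Kaplan-Meier is the only estimator named for the secondary local and distant control endpoints; if deaths are censored, its complement overstates 1-year relapse risk, for local relapse by roughly 2 to 7 points

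*Protocol article*

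**What the plan says.** The Secondary analyses section of the protocol article assigns one method to three endpoints: "The analysis of survival data (evaluation of local control, distant control, and overall survival) will be carried out using the Kaplan-Meier method". Predictive factors are sought with a "Cox proportional hazards model (uni- and multivariate regression, possibly LASSO-penalized) to search for predictive factors".

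The event is defined under the primary objective: "Local relapse is defined as the emergence or progression of nodular contrast within the resection cavity according to the RANO-BM criteria". Death is not part of it; death from any cause is the event for overall survival. The 1-year endpoint reads: "At the M12 follow-up visit (i.e. 12 months after preoperative SRT), local control will be evaluated on cerebral MRI".

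No section names cumulative incidence, Fine-Gray or any other competing-risk method, and none says how a death without relapse enters the local or distant control curves.

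**The concern.** A patient who dies without relapse can no longer relapse. If that death is treated as ordinary censoring, Kaplan-Meier describes relapse in a hypothetical population in which nobody dies first. Its complement is then never below the proportion of patients who actually relapse, and it exceeds that proportion once relapses follow deaths.

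The gap grows with mortality, and mortality here is unlikely to be negligible. The cited retrospective preoperative series "showed 6-month and 12-month survival rates of 77,8 and 60% respectively". Applied to 70 patients, that would be 70 × 0.40 = 28 deaths by M12. The trial presents preoperative SRT as an alternative to postoperative SRT, and readers will take the 1-year relapse figures as absolute risks.

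**Working it through.** The plan gives no figure of its own for this point, so there is none to reproduce. The check sizes the gap between one minus Kaplan-Meier (1 − KM) and cumulative incidence.

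**Inputs from the protocol**
- Survival after preoperative SRT: 77.8% at 6 months and 60% at 12 months (Background, one series of 47 patients).
- Local control in that series: "The six-month local control rate was 97,8%, falling to 85,6% and 71,8% at 12 and 24 months respectively".
- Postoperative studies: "have shown an estimated local control rate of 70% at 6 months and 62% at one year".
- 6-month control of 86% (design alternative) and 80% (the 56/70 success boundary), from Sample size.

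**Assumptions**
- Relapse and death hazards are independent and constant within 0–6 and 6–12 months.
- The control rates are read as Kaplan-Meier rates with deaths censored. The protocol does not say how they were estimated.
- For 86% and 80%, the 6-month hazard continues to 12 months, so 12-month control is 0.86² = 74.0% and 0.80² = 64.0%.
- Two better survival patterns are assumed for the range: 85%/70% and 90%/80% at 6/12 months.

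**Formulas.** Let L1, L2 be the cumulative relapse hazards and D1, D2 the cumulative death hazards in the two half-years.
- CIF(6) = L1/(L1+D1) × [1 − exp(−(L1+D1))]
- CIF(12) = CIF(6) + exp(−(L1+D1)) × L2/(L2+D2) × [1 − exp(−(L2+D2))]

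**Worked case: control 70%/62%, survival 77.8%/60%**
- L1 = −ln 0.70 = 0.357; L2 = −ln(0.62/0.70) = 0.121
- D1 = −ln 0.778 = 0.251; D2 = −ln(0.60/0.778) = 0.260
- Alive and relapse-free at 6 months: 0.70 × 0.778 = 0.545
- CIF(6) = (0.357/0.608) × (1 − 0.545) = 0.267, against 1 − KM of 0.300
- CIF(12) = 0.267 + 0.545 × (0.121/0.381) × (1 − e^(−0.381)) = 0.267 + 0.055 = 0.322, against 1 − KM of 0.380

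**Local relapse at 12 months** (gap in points, from unrounded values)

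| Control at 6/12 months | 1 − KM | CIF, survival 60% | CIF, survival 70% | CIF, survival 80% |
|---|---|---|---|---|
| 70% / 62% | 38.0% | 32.2% (5.8) | 34.0% (4.0) | 35.4% (2.6) |
| 97.8% / 85.6% | 14.4% | 10.3% (4.1) | 11.5% (2.9) | 12.5% (1.9) |
| 86% / 74.0% | 26.0% | 20.7% (5.3) | 22.3% (3.8) | 23.5% (2.5) |
| 80% / 64.0% | 36.0% | 28.8% (7.2) | 30.9% (5.1) | 32.6% (3.4) |

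At 60% survival the overstatement is 4.1 to 7.2 points. Relative to the cumulative incidence, it runs from 18% (5.8/32.2) to 39% (4.07/10.33, unrounded). In 70 patients it is about 3 to 5 people (70 × 0.041 = 2.9; 70 × 0.072 = 5.0). At 6 months, with 77.8% survival, the gap is only 0.3 to 3.3 points.

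No distant-control rate appears in the document, so the same calculation cannot be made for distant relapse.

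**The case against.** The strongest case on the other side has four parts.

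**The censoring rule is inferred.** No section states it, and such rules are often left to the full protocol or SAP. This stands as a caveat. However, counting death as failure would give relapse-free survival, which is not the endpoint named, and the choice of estimator is stated rather than omitted.

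**Kaplan-Meier can be a legitimate target.** With deaths censored, Kaplan-Meier and Cox address the relapse hazard, which is a recognised target for a local treatment, and the protocol does not promise to report 1 − KM as the proportion relapsing. This is a reason to keep Kaplan-Meier, but not to have it as the sole estimate of 1-year control.

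**No decision turns on it.** A reader might infer that the verdict on preoperative SRT rests on these curves. The document does not support that. The rules are at least 56/70 with local control at 6 months and at most 5/70 with radio-necrosis, and neither uses the secondary estimates. The Primary analysis section does turn to Kaplan-Meier when patients are not assessable, but how early deaths enter that rate is a separate question. The bias also understates control, which is conservative for an efficacy claim.

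**The mortality is borrowed.** A reader might take 40% deaths by 12 months as the trial's expectation. It is the complement of one retrospective series' survival; the trial states none and requires "Estimated overall survival ≥6 months according to DS GPA", which may lower mortality. The gap shrinks accordingly but stays positive.

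A reader might also suppose that distant relapse is the worst affected. Without a distant-relapse rate in the document, that cannot be shown.

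**Conclusion.** The point holds as a reporting defect in the secondary analyses. If deaths without relapse are censored, as the event definition implies, the planned estimator overstates 12-month local relapse by about 4 to 7 points at 60% survival, 3 to 5 points at 70% and 2 to 3 points at 80%. The direction does not depend on the hazard model. The size does, and it rests on independent, piecewise-constant hazards and on survival figures that are not the trial's own. The first row of the table also combines postoperative control with preoperative survival, so it is an illustration and not a forecast.

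What is affected is the absolute 1-year relapse risk given to readers. The sample size and both decision rules are untouched. Because the estimation scale of the 70% and 62% benchmarks is not stated, the net effect on a comparison with them is unknown.

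**What to change.** - State how a death without relapse is handled in the local and distant control analyses.
- Add Aalen-Johansen cumulative incidence at 6 and 12 months for local and distant relapse, with death without relapse as the competing event. Use the same estimator for leptomeningeal relapse if it is analysed as time-to-event; the protocol does not assign Kaplan-Meier to that endpoint.
- Report Kaplan-Meier beside it for comparison with the 70% and 62% benchmarks.
- Label the Cox models for local and distant control as cause-specific.

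Vital status is already collected at each time-point, so no new data are needed. The cost is a few lines of code and one more column in the tables. The downside is that the report must explain two estimates of the same endpoint.
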